### Moderators

Current study will include possible moderators, like initial psychological problems, EF, and gender.

*Initial psychological problems* will be assessed by the Dutch version of the Child Behavior Checklist [1, 141], which is a parent-report questionnaire on adolescents’ internalizing and externalizing symptoms. Parents are asked to score 113 problem items which were presented (0), sometimes presented (1), or very often present (2) in the past 6 months, and can be divided into eight subscales, namely. Anxiety/depressive, withdrawal/depressive, somatic complaints, social problems, thought problems, attention problems, antisocial behavior, and aggressive behavior. The scores on these subscales can be summed up to yield total scores on internalizing problems, externalizing problems, and total problem level [1, 141]. The CBCL is a well validated and reliable questionnaire [1, 141].

*EF* will be assessed by the Dutch parent version of the Behavior Rating Inventory of Executive Functioning (BRIEF) [60, 126]. The BRIEF parent version aims to assess adolescents’ everyday EF by asking parents to score their child’s behavior on a 3-point Likert scale, ranging from ‘never’ to ‘frequently’. The questionnaire consists of 86 items that can be divided into eight subscales, namely *inhibition, shifting, emotional control, initiation, working memory, planning/organizing, organizing materials,* and *monitoring.* In current study, the global executive score will be used. Higher scores indicate weaker executive functioning. The BRIEF has revealed a good reliability and validity [126].

Finally, information on socio-demographic factors including *gender* will also be obtained from both child and parents.

### Feasibility indices

Fidelity and treatment integrity of the trainers will be assessed to estimate the feasibility of the program. Each trainer will be asked to indicate to what extent the program has been followed, the goals that have been reached, and how well they were able to guide and help the adolescents during the Boost Camp program. Further, trainers and adolescents will fill out an evaluation form about their experience of the Boost camp program with regard to the group atmosphere, adolescents’ motivation and program comprehensibility. Lastly, the program components will be taped and scored by independent coders in order to check feasibility. An overview of measurements and time points can be found in Table 1.

**Table 1 Tab1:** An overview of measurements and time points

Concept	Measurement (items)	Measurement in time points			
		T0	T1	T2	T3
Primary outcome measure					
ER					
Emotional awareness	DERS	x	x	x	x
ER strategies	FEEL-KJ	x		x	x
Emotional wellbeing					
Positive and negative affect	PANAS-C	x	x	x	x
Self-esteem	CBSA	x	x	x	x
Quality of Life	HRQoL	x		x	x
Depressive symptoms	CDI	x	x	x	x
	CES-D	x	x	x	x
Anxiety symptoms	STAI-C	x	x	x	x
Secondary outcome measure					
Social behavior					
Attitudes about stigmatization	SSRPH	x	x	x	x
Relationship with peers and bullying	OBVQ	x	x	x	x
Academic Performance					
School achievement	ARSP	x			x
	Self-report question	x			x
	School Orientation Attest				x
School drop-out	School data				x
School absence	School data				x
Moderators					
Initial psychological problems	CBCL	x			x
Executive functioning	BRIEF	x			x
Gender	Self-report question	x			

Note: FEEL-KJ = the Fragebogen zur Erhebung der Emotionsregulation bei Kindern und Jugendlichen [22], DERS = Difficulties in Emotion Regulation Scale [62], PANAS = Positive And Negative Affect Schedule for Children [88], CDI = Children’s Depression Inventory [85], CES-D = Center for Epidemiological Studies Depression Scale [109], STAI-C = State-Trate Anxiety Inventory for Children [7], CBSA = Competence Belief Scale for Adolescents [139], HRQoL = KIDSCREEN-10 well-being and health-related quality of life [112], CBCL = Child Behavior CheckList [141], OBVQ = Olweus Bully/Victim Questionnaire [91], SSRPH = Stigma Scale for Receiving Psychological Help [106], ARSP = Academic Performance Rating Scale [50], BRIEF = Behavior Rating Inventory for Executive Function [60] T0 = Baseline assessment, T1 = Post-test, T2 = 3 months follow-up, T3 = 6 months follow-up

### Data analysis

Power analyses were calculated to determine the required sample size for detecting a clinically significant difference between the intervention and control group at 6 months follow-up on one primary outcome (FEEL-KJ). With a significance level of α = 0.05 and a power level of β = 0.90, a total sample of 86 N_Non-cluster_ participants is needed to detect a significant difference. However, the clustering of participants within schools has to be considered and therefore, the design effect is calculated as 1 + (m-1)*ICC, with m referring to the number of participants per cluster [57]. Based on prior research determining the ICC values for adolescent health outcomes [121], an Intraclass Correlation Coefficient (ICC) of 0.02 was used. The estimated average size of the classes participating in current study is counted on 20 students per class, resulting in a design effect of 1,38. Moreover, as the intervention requires a high time investment, an 3:2 ratio in favor of the control group will be chosen at randomization. Following the recommendations of Gao et al. [57], the final calculation of the total sample of the control group was multiplied by the design effect with the randomization ratio and the N_Non-Cluster,_ resulting in a total sample size of 241 students, 145 for the control group and 97 for the intervention group. Taking into account declined participation and loss to follow-up, a drop-out rate of 20% is estimated. Finally, this resulted in a required sample size of 291 students, 174 in the control group and 117 in the intervention group, clustered in at least 16 classes.

Assumptions will be checked by examining descriptive statistics and missing variables will be examined. When data are missing completely at random, maximum likelihood estimation will be used to estimate the missing values. When data are not missing completely at random, generalized estimating equation analyses will be used. Possible baseline differences in both groups will be assessed using simple t-tests or chi-square tests, and variables that show baseline differences will be entered as covariates of no interest in all models. To assess the difference between the intervention and control condition in the change in the use of adaptive ER skills and in emotional wellbeing during 6 months following the program, a mixed model will be used. More specifically, a mixed model with fixed effects for condition (intervention or control), time (immediately after intervention, 2 months post FU, and 6 months post FU), and their interaction, adjusted for baseline will be used. Moderators will be added one by one. To account for the nested structure of students within classes, and classes within schools, a random intercept for schools and a random intercept for classes nested within schools will be utilized. To account for the temporal correlation of measurements within a student, an unstructured residual covariance will be assumed.

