**Methods:**

The aim is to reach 300 adolescents (16 class groups, 6 schools) in their first year of high school. A clustered Randomized Controlled Trial (RCT) with two conditions, intervention (*n* = 150) and control (n = 150), will be set up. Adolescents in the intervention condition will receive 14 lessons over the course of 2 days, followed by Booster sessions, and will be compared with adolescents in a non-intervention control group. The outcomes will be measured by self-report questionnaires at baseline, immediately after Boost camp, and at three and 6 months follow-up.

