### Design

The effectiveness of Boost Camp will be tested by a clustered randomized controlled trial (cRCT) with two conditions, e.g. an intervention and a control condition (see Fig. 1). Randomization is clustered by school, which reduces the risk of contamination.

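### The design effect takes the class as the cluster although six whole schools are randomised, and six schools do not give the stated 90% power

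*Protocol article*

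**What the plan says.** The unit of randomisation is explicit in the Design section: "Randomization is clustered by school, which reduces the risk of contamination". Participants and procedure also has consenting schools being randomised, six of which took part. The abstract gives the planned size: "The aim is to reach 300 adolescents (16 class groups, 6 schools) in their first year of high school".

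The sample-size paragraph under Data analysis begins from "With a significance level of α = 0.05 and a power level of β = 0.90" (the 0.90 is evidently power) and states that "a total sample of 86 N_Non-cluster_ participants is needed to detect a significant difference". It then says that "the clustering of participants within schools has to be considered", and that "the design effect is calculated as 1 + (m-1)*ICC, with m referring to the number of participants per cluster". The ICC is 0.02, taken from earlier research, with no statement of whether it is a school or a class value. The cluster size entered is the class: "counted on 20 students per class, resulting in a design effect of 1,38". With a 3:2 ratio in favour of control this leads to 241 students (145 and 97), and to 291 (174 and 117) after an allowance for 20% loss.

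The next paragraph of Data analysis specifies a mixed model adjusted for baseline, with random intercepts at both school and class level. It names no reference distribution for the test of condition.

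**The concern.** In a cluster-randomised trial, the design effect must reflect the unit that was randomised. Here that unit is the school, the paragraph itself names the school as the level to allow for, and m is defined as participants per cluster. Classes are not randomised, so 20 is not the size of the randomised cluster. The planned model also allows for a school variance component that the sample size leaves out.

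A second feature points the same way. The calculation treats the number of clusters as large, but six schools in two arms leave 6 - 2 = 4 degrees of freedom for comparing conditions.

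At stake is how the result is read. A null finding would be presented as coming from a trial with 90% power when the design gives less.

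**Working it through.** **Inputs from the article:** two arms; six schools; 300 students enrolled; 20% loss, so 240 analysed; ICC 0.02; alpha 0.05 (taken as two-sided); m = 20; unclustered N = 86; 3:2 ratio in the sample-size paragraph, 150 per arm in the abstract.

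**Assumptions:** six schools of equal size; ICC 0.02 is a school-level value; 86 is per arm.

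**1. The plan's own figures.** The design effect is 1 + (20 - 1) × 0.02 = 1.38, as printed. No effect size is given. At d = 0.5 the normal approximation needs 2 × (1.960 + 1.282)² / 0.25 = 84.06 per arm, and a t-test with 86 per arm has power 0.903. With 3:2 allocation, control = n × 1.38 × (1 + 1.5)/2 and intervention = n × 1.38 × (1 + 1/1.5)/2:

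- n = 84.06: 145.0 + 96.7 = 241.7
- n = 86: 148.4 + 98.9 = 247.3
- 86 as a total: 86 × 1.38 = 119 with equal arms, or about 124 with 3:2

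The printed 241 can therefore be approximated only if 86 is per arm, although the text calls it a total.

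**2. Design effect with the school as cluster.**

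- Analysed: m = 240/6 = 40, so 1 + 39 × 0.02 = 1.78
- Enrolled: m = 300/6 = 50, so 1 + 49 × 0.02 = 1.98

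**3. Power at 240 analysed, d = 0.5.** Variance = DE × (1/n1 + 1/n2); noncentrality = 0.5/√variance. For DE 1.78 and 120 per arm, the variance is 0.02967 and the noncentrality 2.90. The critical value is 1.96 (normal) or 2.776 (t on 4 df).

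| Design effect | Arms | Normal | t, 4 df |
|---|---|---|---|
| 1.38 (as planned) | 1:1 | 91% | 70% |
| 1.38 (as planned) | 3:2 | 90% | 68% |
| 1.78 (school, ICC 0.02) | 1:1 | 83% | 59% |
| 1.78 (school, ICC 0.02) | 3:2 | 81% | 58% |
| 1.39 (school, ICC 0.01) | 1:1 | 91% | 69% |
| 2.95 (school, ICC 0.05) | 1:1 | 62% | 41% |

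The value 1.98 belongs with 300 students and no loss, where power is 85-87% (normal) or 62-64% (4 df).

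**4. A check that needs no effect size.** If DE 1.38 gave exactly 90%, the noncentrality at another DE is 3.242 × √(1.38/DE). At 1.78 it is 2.85, which gives 81% (normal) or 58% (4 df).

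**5. Detectable difference.** With DE 1.78, 120 per arm and 4 df, 90% power needs a noncentrality of about 4.40, so 4.40 × √0.02967 = 0.76 SD.

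**6. Baseline adjustment.** If it removed 25% of the variance, the noncentrality would be 2.90/√0.75 = 3.35. Power would be 92% (normal) or 71% (4 df).

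**7. Type I error with a normal reference.** I simulated six schools of 40, with REML and the school variance bounded at zero (class effect ignored). The error rate is about 6% at ICC 0.01, 8% at 0.02 and 10% at 0.05.

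**The case against.** **The ICC may not be a school value.** The article does not state its level. A design effect of 1.38 at m = 40 corresponds to a school ICC of 0.38/39 = 0.0097. If the school ICC is at or below that, using the class size costs almost nothing by normal approximation. This stands. It does not restore 90%, because 4 degrees of freedom still give about 69%.

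**The effect size is inferred.** Read literally, a total of 86 implies d of about 0.70. Power at DE 1.78 would then be about 98% (normal) and 83-86% (4 df). That reading cannot produce 241, so the per-arm reading is the more credible one, but every power figure at d = 0.5 depends on it.

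**Baseline adjustment may recover power.** It may: an assumed baseline correlation of 0.7 would bring power on 4 df to about 85%. The sample-size paragraph claims no such gain.

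Three stronger readings are tempting but not supported:

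- A reader might put the whole fall from 90% to 59% down to the wrong cluster size. Correcting m alone moves normal-approximation power only from about 90-91% to 81-83%; the rest comes from having six schools.
- A reader might infer a 12% type I error, since 2 × P(t on 4 df > 1.96) = 0.122. That describes a test on school means with unconstrained between-school variance. For the planned mixed model, where a small school variance estimate is bounded at zero, about 6-10% is the better figure.
- A reader might fault the article for ignoring schools at analysis or for naming no degrees-of-freedom method. The model has a school random intercept, and the method can properly be left to an analysis plan. The inflation arises only if a normal reference is used.

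**Conclusion.** The point holds. The arithmetic of 1.38 is correct, but its m is not the size of the randomised cluster that the same paragraph says must be considered. If ICC 0.02 is school-level and 86 is per arm, the design effect is 1.78-1.98 and power at about 240 analysed is 81-83% by normal approximation.

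With the 4 degrees of freedom that six schools allow, power is about 58-59%, ranging from 69% at ICC 0.01 to 41% at ICC 0.05. At low school ICC the shortfall is due to the number of schools rather than to the design effect.

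Low power does not bias the estimate. The fault is a stated 90% that the design does not deliver.

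**What to change.** In the sample-size paragraph:

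- Recompute the design effect with m = students per school, or use a three-level form with separate school and class ICCs, and state the level of the 0.02.
- State whether 86 is per arm or a total, and give the difference assumed.
- Restate the power, or the difference detectable with 90% power, that six schools give. Use a t reference on 4 degrees of freedom and show ICC 0.01 to 0.05. If credit is taken for baseline adjustment, state the assumed variance reduction.

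In the analysis: keep the school and class random intercepts, and add that condition is tested with small-sample degrees of freedom, for example Kenward-Roger.

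The cost is one rewritten paragraph and one added line. No extra schools are needed; the downside is a less favourable stated power.

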## Methods

### Participants and procedure

Six secondary schools in the East of Flanders are contacted to participate in the study. Participants are adolescents in their first year of secondary school (7th grade, ages 11–13). The aim is to reach 300 students spread over 16 classes. We ensure the inclusion of students from different Socio Economic Status (SES) groups and various educational levels to compose a heterogeneous sample. In Belgium, there are two educational levels in secondary school. The first education level, grade A, is considered as a broad first grade in which students receive basic knowledge on technics, mathematics, or languages, with the intention to prepare them on a more specific educational program in the second grade. The second education level, grade B, is intended for students with specific needs. Both are included.

Schools that are interested are asked to participate with as many first-grade class groups as possible. If they give their consent to take part in the study, they are randomized by the researcher in a intervention or a control group. Finally, six rural schools with comparable background and meeting the same language criteria decided to participate in the study. All schools receive information letters for students and their parents, which contain detailed information about the study aims and procedure. Parents can either give or withhold their permission for including their child’s data in the study, and both parents and children are free to withdraw from the study at all times. The Boost Camp program is incorporated in the class curriculum, so all participants in the intervention condition receive the program. The advantage of incorporating the program in the class curriculum is that all adolescents participate and interact. To ensure that the intervention and the control schools place an equal emphasis on students’ mental health, teachers of all participating schools receive a workshop on care management and are invited to sign a school charter on the importance of emotional well-being of the schoolchildren.

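### The article gives two incompatible allocations, 150:150 and 3:2 (174:117), and does not say how six randomised schools are divided between the arms

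*Protocol article*

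**What the plan says.** The Methods paragraph of the abstract in the protocol article plans "two conditions, intervention (*n* = 150) and control (n = 150), will be set up", with a target of 300 adolescents in 16 classes and 6 schools. That is 1:1.

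The Data analysis section says that "an 3:2 ratio in favor of the control group will be chosen at randomization". The reason given is that the intervention takes a lot of time. The ratio is then used in the calculation, which gives "a total sample size of 241 students, 145 for the control group and 97 for the intervention group" before drop-out and "a required sample size of 291 students, 174 in the control group and 117 in the intervention group, clustered in at least 16 classes" after it.

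The unit of randomisation is the school. The Design section says "Randomization is clustered by school, which reduces the risk of contamination". Participants and procedure says of the schools: "If they give their consent to take part in the study, they are randomized by the researcher in a intervention or a control group". The same section reports that six schools took part. The article does not state the number of schools allocated to each arm.

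**The concern.** The allocation ratio is a basic design parameter, and here it has two values, both written as current. One is used to describe the trial and the other to size it. The article does not reconcile them.

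The 3:2 ratio is placed at randomisation, so it reads as a property of the draw. The draw, however, is of six schools. A reader cannot tell whether the plan was three schools against three, four against two, or something else. Nor can a reader later judge whether the arms obtained match the plan. The required arm sizes are also tied to a ratio that the abstract does not use.

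**Working it through.** **1. Is 3:2 a slip or part of the calculation?** Inputs from Data analysis: unclustered N = 86, ICC 0.02, 20 students per class, 20% drop-out.

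- Design effect: 1 + (20 − 1) × 0.02 = 1.38, as stated.
- Arm sizes at ratio r = 1.5, with n per arm under 1:1: control = n × 1.38 × (1 + r)/2; intervention = control/r.
- n = 86 per arm: 148.4 control, 98.9 intervention, total 247.3. This is within 3% of the stated 145, 97 and 241.
- n = 84 per arm: 144.9, 96.6, total 241.5, which is almost exactly as stated.
- Drop-out: 145 × 1.2 = 174; 97 × 1.2 = 116.4, rounded up to 117; total 291, as stated.
- Ratios: 145/97 = 1.495 and 174/117 = 1.487.

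The 3:2 ratio therefore runs through the whole calculation and is not a stray phrase. (The article calls 86 a total, but its figures follow only if 86 is read as per arm. That is a separate matter.)

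**2. Does rounding 291 up to 300 explain the abstract?** No. 300 × 3/5 = 180 and 300 × 2/5 = 120, not 150 and 150. Against the Data analysis figures, the abstract's control arm is 174 − 150 = 24 smaller and its intervention arm 150 − 117 = 33 larger.

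**3. Can six schools be split 3:2?** 6 × 3/5 = 3.6 and 6 × 2/5 = 2.4. The whole-number splits are 3:3 (ratio 1), 4:2 (ratio 2) and 5:1 (ratio 5). Sixteen classes do not divide exactly either (9.6:6.4). The nearest class splits are 9:7 (1.29) and 10:6 (1.67).

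**4. Does the conflict cost power on the article's own terms?** Each arm is multiplied by 0.8 for loss and divided by 1.38. The test is taken as two-sided at 0.05 with a normal approximation. The standardised difference d is an assumption, because the article states none.

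SE = √[(1.38/0.8) × (1/a + 1/b)], where a and b are the arm sizes.

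- 150:150: SE = 0.1517
- 174:117: SE = 0.1570

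| Assumed d | Power, 150:150 | Power, 174:117 |
|---|---|---|
| 0.3 | 0.51 | 0.48 |
| 0.4 | 0.75 | 0.72 |
| 0.5 | 0.91 | 0.89 |

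The variance for 174:117 is (1/174 + 1/117)/(1/150 + 1/150) = 1.07 times that for 150:150.

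**5. What if the 3:2 intention led to a 4:2 draw of schools?** The documents do not mention such a draw, so this is a what-if.

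- Variance factor for the school contrast: 3:3 gives 1/3 + 1/3 = 0.667; 4:2 gives 1/4 + 1/2 = 0.750. The ratio is 1.125, or 12.5% more variance.
- Power from the non-central t with 4 df, assuming ICC 0.02 between schools, 240 students analysed and equal schools of 40. The variance of a school mean is 0.02 + 0.98/40 = 0.0445.

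| Assumed d | 3:3 | 4:2 | Difference |
|---|---|---|---|
| 0.3 | 0.269 | 0.245 | 0.024 |
| 0.4 | 0.426 | 0.388 | 0.038 |
| 0.5 | 0.592 | 0.546 | 0.047 |
| 0.6 | 0.741 | 0.694 | 0.048 |

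Only the differences bear on allocation. The low level in both columns comes from analysing six schools with 4 df, whichever way they are split.

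**The case against.** The best reply is that 3:2 is expressed in students, not schools. Schools were asked to bring as many first-year classes as they could, and 16 classes cannot be spread equally over six schools. A 3:3 split with about 10 classes against 6, or a 4:2 split with larger intervention schools, could give roughly 3:2 in students. This stands as far as it goes. A reader might infer that a 3:2 allocation is flatly impossible, but only an exact split by number of schools is. The reply still leaves the gap open. The article describes no mechanism for reaching 3:2 through school size, and a ratio that emerged that way would still contradict 150:150.

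A second reply is that the trial is not short of students: 300 exceeds the required 291, and equal arms are the more efficient. This stands in full. A reader might infer from the control arm's shortfall of 24 that the trial is under-sized. The comparison of power in step 4 shows the opposite, because the 33 extra intervention students more than make up for it.

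A third reply is that unequal allocation has a stated reason, the time the intervention requires. That also stands, so the correction should not presume that 1:1 is the intended design.

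**Conclusion.** The contradiction is real: 1:1 with 150 per arm in the abstract, 3:2 with 174 and 117 in Data analysis, and no number of schools per arm anywhere. An exact 3:2 split of the six randomised schools does not exist.

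The statistical consequence is small. On the article's own design effect and loss rate, 150:150 gains about 2 to 3 percentage points of power over 174:117 for assumed d from 0.3 to 0.5.

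A reader might go further and conclude that the trial loses precision through a 4:2 draw with only two intervention schools. The documents do not support that, because no 4:2 draw is mentioned. If one had occurred, it would add 12.5% to the variance of the school contrast and cost about 2 to 5 points of power relative to 3:3, for assumed d from 0.3 to 0.6 and under the assumptions shown in step 5.

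The point is worth correcting because a figure on which the sizing rests is wrong in one of the two places, and the correction is cheap.

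**What to change.** State the number of schools in each arm and the intended student ratio. Use that one allocation in both the abstract and the Data analysis section, and recompute the required arm sizes for it.

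- If the schools are split 3:3 with 150:150 students, drop the 3:2 factor from the calculation.
- If unequal allocation is kept because of the intervention's time demands, correct the abstract's 150:150 and size the trial for a school split that can be drawn, for example 4:2 (2:1).
- If a student ratio near 3:2 is meant to come from unequal school sizes, say how the draw secures it.

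The cost is a text correction and a short recalculation. Schools that have already been randomised stay where they are; the text should report the split that was drawn.

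### The sample-size chain does not follow from its own inputs: 86 as a total cannot give 241, and the 20% loss is multiplied in instead of divided out

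*Protocol article*

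**What the plan says.** The Data analysis section sizes the trial on the FEEL-KJ at 6 months. Its steps are:

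- Error rates: "With a significance level of α = 0.05 and a power level of β = 0.90" (0.90 is evidently the power; sidedness is not given).
- Unclustered size: "a total sample of 86".
- Clustering: "the design effect is calculated as 1 + (m-1)*ICC", with 20 students per class, and "an Intraclass Correlation Coefficient (ICC) of 0.02 was used". The design effect is reported as 1.38.
- Allocation: 3:2 in favour of control, using a cited method for unequal arms.
- Clustered size: "resulting in a total sample size of 241 students, 145 for the control group and 97 for the intervention group".
- Loss: "a drop-out rate of 20% is estimated".
- Final size: "this resulted in a required sample size of 291 students, 174 in the control group and 117 in the intervention group".

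The article gives no target difference and no standard deviation for the FEEL-KJ. The Abstract and the Participants and procedure section set a recruitment target of 300.

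**The concern.** Two steps do not follow from the figures before them. The step from 86 to 241 is a factor of about 2.8, while the only multipliers given are a design effect of 1.38 and a mild penalty for 3:2 allocation. The step from 241 to 291 does not leave 241 students after a 20% loss.

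The first step carries the weight. Because the article gives no target difference, the figure of 86 is the reader's only clue to the effect the trial was sized to detect. If its label is wrong, a reader who works back from it will misjudge what the trial could detect, and may then misread a null or moderate result. The second step means that the stated requirement does not meet its own condition.

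**Working it through.** **Inputs.** From the Data analysis section: alpha 0.05, power 0.90, N = 86, m = 20, ICC = 0.02, control:intervention = 3:2, loss 20%. Assumed, because the article does not state them: two-sided testing and, where marked, a standardised difference d = 0.5.

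**Design effect.** 1 + (20 − 1) × 0.02 = 1.38. This reproduces.

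**From 86 to 241.** With ratio r = 1.5 the allocation penalty is (1 + r)²/(4r) = 6.25/6 = 1.0417.

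| Reading of 86 | × 1.38 | × 1.38 × 1.0417 | Control / intervention |
|---|---|---|---|
| Total (86) | 118.7 | 123.6 | 74.2 / 49.5 |
| Per group (172 in total) | 237.4 | 247.3 | 148.4 / 98.9 |
| Stated | | 241 | 145 / 97 |

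As a total, 86 gives about half of the stated figure. As a per-group number it comes within 3% of 241, but it does not reproduce 145/97. Multiplying 86 directly by the design effect and the ratio does not give the control arm either: 86 × 1.38 × 1.5 = 178.

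**What does give 145/97.** Assume d = 0.5 and the normal approximation:

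- Per group at 1:1: 2 × (1.960 + 1.282)²/0.5² = 84.06.
- Control at 3:2: 84.06 × 1.25 = 105.07; × 1.38 = 145.0.
- Intervention at 3:2: 84.06 × 5/6 = 70.05; × 1.38 = 96.7.
- Sum: 241.7.

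This matches the stated arms. The t-test size for the same d is 85.03 per group, which rounds up to 86. A per-group 86 from a t-test, followed by 145/97 from the unrounded normal formula, would therefore explain every figure. That is an inference from the numbers, not something the article says.

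**Difference implied by each reading** (two-sided t-test, 90% power, equal groups):

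- 86 in total, 43 per group: about 0.71 SD.
- 86 per group: about 0.50 SD.

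**Loss.**

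- Method used: 145 × 1.2 = 174; 97 × 1.2 = 116.4, rounded up to 117; sum 291. This reproduces the stated figure exactly.
- What it leaves: 291 × 0.8 = 232.8 (139.2 + 93.6), against 241.
- Division: 241/0.8 = 301.25, so 302. By arm, 145/0.8 = 181.25, so 182, and 97/0.8 = 121.25, so 122; sum 304.
- Target of 300: 300 × 0.8 = 240.

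**Power** (design effect 1.38, assumed d = 0.5, normal approximation):

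| Completers | Power |
|---|---|
| 145 / 97 | 0.901 |
| 139.2 / 93.6 (291 less 20%) | 0.890 |
| 144 / 96 (300 at 3:2, less 20%) | 0.898 |

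**The case against.** The best defence is that 241 is probably right and that one word is wrong. The text describes building the control arm from the unclustered number, the design effect and the ratio by a cited method that is not at hand, and that fits a per-group input. A condensed article may also leave the assumed difference and standard deviation to the full protocol. Both points stand. They limit the concern to a published figure that contradicts the next figures in the same paragraph. The absence of an effect size is not in itself the finding.

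A reader might go further and infer that the trial needs only 119 to 124 students, or that it was sized for 0.71 SD. The documents do not support that, because the 145/97 split points to a per-group figure. A reader might equally want to write in 86 per group and d = 0.5 as the answer. That is not supported either: 86 per group leads to 247, not 241, and d = 0.5 is back-calculated and appears nowhere in the article.

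On the loss step, the defence is that recruitment aims at 300, not 291, so almost all of the shortfall is absorbed. That also stands, and it makes this part minor. A reading that the trial is materially underpowered because of the loss error would be wrong.

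The arms add to 242 against a stated 241. This is rounding (145.0 + 96.7 = 241.7), and it does not carry forward, because 291 is built from the arms.

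**Conclusion.** The chain is wrong as written in two places.

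1. The figure 86, labelled a total, is inconsistent with 241 by a factor of about two. The label is probably the error and 241 probably stands, but only the sponsor can confirm this. Until then the detectable difference is open between about 0.50 and 0.71 SD. Those values assume two-sided testing at 0.05 with 90% power.
2. The loss inflation is certainly a multiplication by 1.2. The stated 291 is 11 to 13 students below the 302 to 304 that a 20% loss requires. Under the assumed d = 0.5 the cost is about one percentage point of power (0.89 against 0.90), and the target of 300 leaves 240, one short of 241.

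The first point justifies a correction; the second belongs in the same edit.

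**What to change.** In the Data analysis section, the sponsor should:

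- confirm whether 86 is per group or in total, and correct the label if needed;
- state the target difference, the sidedness and the formula actually used, so that the path from the unclustered number to 241 can be reproduced;
- replace 291 with 302 (or 304 with each arm rounded up), or keep the target of 300 and state that it leaves 240 after a 20% loss;
- make the two arms and their total agree (241 or 242) in the same edit.

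The cost is the rewording of one paragraph. The stated requirement rises by 11 to 13 students on paper, which is 2 to 4 above the existing target of 300.
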